
**Music and sound sample criteria and choices**

Prior to coming to the experimental site, all subjects will be asked to provide a set of songs (each at least 5.5 minutes long) that they love, have been familiar with for at least a few years but do not tend to get tired of, vary across a range from very relaxing to very energizing, do not evoke specific memories or chills, and that they have not seen the music video for. This list of criteria is designed to maximize our ability to discern the specific effects of subjects’ personal music choices for analgesia. Subjects will be asked to answer a variety of music usage questions prior to starting the study procedures. During Session 1, all subjects will rate their songs in terms of valence and arousal on Self Assessment Manikin (SAM) scales (Bradley and Lang, 1994) and will again be asked if specific memories or chills occur while listening, to screen for these potentially confounding factors16,18. Song excerpts centered on the most favored part of each piece and of length appropriate for the intended pain stimulation will be determined. To match the element of choice present in their personal music, subjects will also have the option of choosing one of two sound samples, both neutrally rated in valence and arousal (validated separately by lab members naive to the nature of the control). The sound samples will be colored noise that is frequency filtered to remove higher frequencies and have previously been perceived to be less distressing than white noise1,5. Subjects will be exposed to the two sound samples during Session 1 to familiarize them with the stimuli. Then, during Session 2, before any experimental trials begin all subjects will first choose the song and sound sample they want to listen to during the pain trials.

**Session 1: Subject screening, pain response characterization, and training**

After giving consent, all subjects will complete self-report baseline assessments (BDI-II, TAS, STAI-State, GSES, RRQ; see descriptions below). Session 1 is made up of **threshold/tolerance acquisition, screening/calibration**, and **rating stability testing**.

Before beginning heat testing, to ensure that sensitization and habituation of the same area of skin will be avoided in successive stimulation sets, lines will be drawn to divide the skin on the palmar surface of the right forearm into four discrete regions (labeled 1-4 in **Figure 1**). Noxious heat stimuli will be delivered using a Thermal Sensory Analyzer (TSA-II) or the Pathway CHEPS model (Contact Heat-Evoked Potential Stimulator) with a 3 cm ´ 3 cm probe (Medoc Advanced Medical Systems, Rimat Yishai, Israel; Biomedical Engineering Device # 1043681 and #1092912, respectively) running proprietary computerized visual analog scale software (COVAS) (This device is currently used in other studies in our lab, including protocols 2009P000096 and 2010P001368).

The purpose of Session 1 is primarily to train subjects to rate their pain using the 0-100 sensory and unpleasantness visual analog scales (VAS, description below), and to determine individually calibrated stimuli temperatures that elicit certain intensity ratings for each subject. The first block of stimuli will be part of **threshold/tolerance acquisition**, during which subjects will first be instructed on how to use the 0-100 VAS to rate the heat stimuli applied to the skin on the back of their right hand. Each subject will use a button press to start and stop the CHEPS device, running a slowly ascending (.5ºC/sec) series, to indicate both their pain threshold (“as soon as you feel pain”) and their pain tolerance (“as much pain as you can tolerate”). We will run 2-3 series for each of their threshold and tolerance levels, switching to adjacent areas of skin on the back of the hand, for a total of 4-6 series that will yield reliable average values for threshold and tolerance. Then, we will perform up to two ascending series of calibrated heat stimuli on region 1 on the palmar surface of the right forearm (See Figure 1). The first stimulus of each ascending series will be initiated from a resting temperature of 32°C and increased to a target temperature of 38°C. The stimulus will be presented for 12 seconds, including 2.5 seconds each for ramp up and ramp down from resting.

[figure not shown]
**Figure 1:**

(Right arm)

[figure not shown]
Subsequent stimuli, separated by a minimum of 30 seconds, will be increased by 1°C until reaching 52°C or the subject’s tolerance. Temperatures that elicit subjective intensity ratings of Moderate = 20-40 and Strong = 60-80 will be selected for each subject for use in Session 2. Once the Moderate and Strong heat pain intensities for a subject have been determined, we will initiate **screening/calibration**.

In the **screening/calibration** block, random sequences of Moderate and Strong intensity noxious stimuli will be administered to regions 2 and 3 (See Figure 1). If the subjects can reliably rate the Strong stimuli as more intense than the Moderate stimuli, they will still be eligible to continue.

Finally, during **rating stability testing**, we will administer 5-6 stimuli on region 4 (Figure 1), all at one temperature that elicitsthe subject’s lower Strong intensity ratings to test whether the subject can consistently rate the same noxious heat stimulation. This is the final test during Session 1 for whether subjects can proceed to Session 2.

During Session 1, subjects will also learn to rate their sense of Perceived Control after pain stimuli using the control subscale of the SAM, their valence and arousal to their chosen music using the SAM, their attention to the audio, and their anxiety during pain stimuli. We will also ask them whether any specific memories or autonomic chills responses occurred during their music, and will ask for a different song sample to be used if this is the case as these are music exclusion criteria in this study (as previously stated). Lastly, subjects will be introduced to both sound samples that they may use during Session 2, and asked to not listen to their music samples on their own until the study concludes.

**Session 2: Expectancy manipulation and testing**

Sessions 1 and 2 will be separated by at least two days (but no more than 10 days) to avoid sensitization to repeated application of the noxious stimuli. Before any pain testing begins in Session 2, subjects will complete the STAI-State and BMIS (descriptions below). The rest of Session 2 is made up of **screening/calibration**, **pre-test/baseline, manipulation** and **post-manipulation test**.

The **screening/calibration** block is the same as that completed in Session 1 to determine eligibility to continue participation in the experiment, with this second pass included to thoroughly check for rating consistency (this procedure significantly improves the quality of the data and interpretability of results). The two sets of random stimuli will be applied to regions labeled ‘RS’ in **Figure 2.** If they pass this screening, they will complete a set of **pre-test/baseline** stimuli of the same procedure as the **rating stability testing** from Session 1, though this time in each of regions 1-3 (Figure 2). Ratings for the first set of baseline stimuli during Session 2 must be within 15% of ratings given during rating stability testing during Session 1 to minimize instability of subject rating across sessions. Throughout the administration of noxious pain sequences, subjects will again rate each stimulus using the 0-100 scales immediately after they are presented. After each set of noxious stimuli, subjects will additionally rate their perceived control, valence/arousal, attention, and anxiety.

[figure not shown]

**Figure 2:**

(Right arm)

Before the experimental manipulation, all subjects will choose the music and sound samples they wish to proceed with in the experiment that day. The two emotionally equivalent samples of sound presented in Session 1 will be re-presented for subjects to choose from. Subjects will not listen to their music samples to determine their choice, but rather will visually pick from their list. They will be given about five minutes to complete this task. Subjects will then be randomized to one of three groups (N=12/group), with the groups characterized by conditioning type (music, sound, or none/routine calibration), for the **manipulation** block. After choosing their sound and music samples, subjects in conditioning groups will be told that during the intended conditioned stimuli (see next paragraph) they may experience less pain. In the calibration group, we will state that *either* their music or the sound may have analgesic effects. Subjects will then fill out the ERS indicating the degree to which they anticipate the “treatment” will work as an analgesic.

Within conditioning groups, we will randomly assign subjects to receive either the conditioned stimuli first, or the non-conditioned stimuli. The conditioned stimuli will consist of lower heat stimuli (the subject’s Moderately rated heat level) paired with either music or sound, and non-conditioned stimuli will consist of the same temperature stimuli used in pre-test/baseline paired with the other audio, sound or music. This conditioning procedure will induce a positive expectancy manipulation in addition to the verbal expectancy introduced earlier. In the calibration group, subjects will experience both heat levels, with either the Moderate or Strong pain stimulus first but without any paired auditory stimuli or specific verbal suggestions. Stimuli during the **manipulation** block will be applied to regions 1-4 on the *left* arm, as seen in **Figure 3**, to avoid over-stimulation of regions on the right arm. After each block of stimuli, subjects in conditioning groups will also be asked to indicate whether any specific memories or autonomic chills responses occurred to their music samples, and all subjects may rate their perceived control, valence/arousal to the audio or silence, attention, and anxiety.

[figure not shown]

**Figure 3:**

(Left arm; pink is lower heat, red is higher heat)

After **manipulation** they will again fill out the ERS, and then continue to the **post-manipulation test**. This is the same as **pre-test/baseline,** except that stimuli are now presented in three contexts: their chosen music, their chosen sound, and silence, with order of presentation randomized across subjects. Stimuli are again applied to regions 1-3 on the right arm (Figure2). After each set of audio/silence + noxious stimuli, subjects will additionally rate their perceived control, valence/arousal to the audio or silence, attention, anxiety, and indicate whether any specific memories or autonomic chills responses occurred.

, Subjects will then fill out another ERS indicating their anticipation of their assigned treatment’s analgesic capacity in future treatments, and complete final questionnaires. At this point we may allow subjects to choose either the sound or music sample they listened to previously, and then we will repeat up to two more stimuli blocks with associated ratings identical to those in the post-test. After completion of Session 2 testing procedures, subjects will be debriefed.

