## **VI. BIOSTATISTICAL ANALYSIS**

**Power Analysis:**
We will study 12 subjects in three groups for a total of 36 subjects; the primary end points are differences between the music/sound conditioning groups and the no conditioning group. In our previous studies for placebo analgesia using a similar model22, 35-37, we observed a SD for pain rating difference of 1.7.  Using this value, with n=12 subjects in each group, we expect 80% power to detect an absolute difference in pain ratings of 2.1 or greater (two sample t-test at the 0.05 two-tailed significance level).

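### Order of music, sound and silence is randomised with no stated balance within groups of 12, and the model has no position term; using each of the six orders twice would be a nearly free gain in precision

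*Protocol*

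**What the plan says.** Protocol section V, Session 2 (post-manipulation test, the text after Figure 3) repeats the baseline heat procedure, except that "stimuli are now presented in three contexts: their chosen music, their chosen sound, and silence", "with order of presentation randomized across subjects". No blocking, counterbalancing or stratification of this order by treatment group is described. The same paragraph adds: "Stimuli are again applied to regions 1-3 on the right arm". Baseline ratings were taken in those same three regions earlier in the session.

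Section VI, Power Analysis, fixes the group size: "We will study 12 subjects in three groups for a total of 36 subjects".

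Section VI, Data analysis, names a repeated-measures ANCOVA with the silence measure as covariate, and conditioning status and audio modality as the factors. It names no order or block-position term.

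The protocol recognises that repeated heat can change the response. In Session 1 the forearm is divided into regions "to ensure that sensitization and habituation of the same area of skin will be avoided in successive stimulation sets", and section VII allows for minor tissue sensitisation.

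**The concern.** Hypothesis 1 (music against sound and silence) and the audio-modality factor are within-subject contrasts between successive heat blocks. If ratings drift from block to block, a context that happens to come later more often in a group carries that drift into its mean. With 12 subjects per group, an unrestricted order list will usually be uneven. Silence is both a comparator and the covariate, so its position matters as well.

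Precision in these contrasts is at stake, and in a small trial it is worth keeping. A model term can still be added in an analysis plan, but the order list must exist before the first subject is tested, and an uneven one cannot be repaired afterwards.

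**Working it through.** **The plan's own figure.** Power Analysis: SD 1.7, difference 2.1, 12 per group, two-sided 0.05, two-sample t-test. The noncentral t gives 82.4% power at n = 12 and 78.7% at n = 11. The stated n reproduces, and the point below does not alter it.

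**Inputs.** From the protocol: three contexts, so 3! = 6 orders; 12 subjects per group; three groups. Assumed, because the protocol gives neither: linear drift of s = 3, 5 or 8 points per block on the 0-100 scale, and an SD of the paired music-sound difference of 10 or 15 points. The counts in steps 1 and 2 also assume an unrestricted (simple) order randomisation.

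**1. Chance of full balance.** 12 / 6 = 2, so each order can be used exactly twice. By chance, P = 12! / (2^6 × 6^12) = 0.0034, or 0.34% per group. The probability that at least one order is never used in a group is 56%.

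**2. Music before sound.** The count is Binomial(12, 0.5).
- 8-4 or worse: 2 × 794/4096 = 0.388 per group; in at least one of three groups, 1 − 0.612³ = 0.770.
- 9-3 or worse: 2 × 299/4096 = 0.146 per group; in at least one of three groups, 0.377.

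**3. Noise from drift, no position term.** Over the six orders, the music and sound positions differ by ±1 in four and by ±2 in two. The mean square is (4 × 1 + 2 × 4)/6 = 2. Drift therefore adds 2s²/12 to the variance SD²/12 of a within-group contrast.
- SD of the chance shift = s√(2/12) = 0.41s: 1.2, 2.0 and 3.3 points for s = 3, 5 and 8.
- Ratio of standard errors = √(1 + 2s²/SD²):

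| s (assumed) | SD of paired difference 10 | SD of paired difference 15 |
|---|---|---|
| 0 | 1.00 | 1.00 |
| 3 | √1.18 = 1.09 | √1.08 = 1.04 |
| 5 | √1.50 = 1.22 | √1.22 = 1.11 |
| 8 | √2.28 = 1.51 | √1.57 = 1.25 |

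The SD here is that of the paired difference. If 10 or 15 were instead the residual SD of a single within-subject rating, the paired difference would have variance 2 × SD², and the increases would be about 4%, 12% and 28% (SD 10) or 2%, 5% and 13% (SD 15).

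**4. With position in the model.** Least squares with subject and position effects, over 3,000 random designs, gives the variance of the music-sound contrast relative to the balanced design:
- n = 12: mean 1.10, median 1.06, 95th percentile 1.34. The mean corresponds to about 5% in the standard error.
- n = 36 pooled: mean 1.03, 95th percentile 1.09.
- Balanced list: 1.00.

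This check treats all three contexts as responses. The protocol's model uses silence as a covariate, so the exact figure there may differ.

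**5. Between-group comparison.** One context's position effect has variance (s² + 0 + s²)/3 = 2s²/3. With an assumed SD of 17 on the 0-100 scale, √(1 + 2s²/(3 × 17²)) = 1.01, 1.03 and 1.07 for s = 3, 5 and 8.

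**The case against.** **The type of randomisation is not stated.** A reader might infer that the protocol prescribes simple randomisation. It does not: the wording also fits a blocked or counterbalanced list, and the 0.34% and 39% figures hold only if the list is unrestricted. This stands. The point is that no balance is stated, not that imbalance is certain.

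**Skin region.** A reader might also infer that skin region is unbalanced across contexts. The documents do not support that. The text does not say how regions map to contexts, Figure 2 cannot be seen here, and baseline is taken in the same regions 1-3, so a pre-minus-post outcome paired by region can remove stable differences between regions.

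**Drift.** The passage on sensitisation and habituation describes a precaution, and no amount of drift is given. This stands: the inflations are conditional on an assumed range that includes zero.

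**Bias.** A reader might see the chance shift as bias. It is not. Randomised order leaves the contrasts unbiased over randomisations, and the shift is sampling noise.

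**Most of the gain comes from the model.** This is largely true. With position adjusted, an uneven list costs only about 10% in variance per group, and a position term could be left to an analysis plan. The list cannot be left that late. Balance without the term would also leave order variation in the error.

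**The primary comparison.** It is between groups and loses only 1-7% in standard error under the assumptions of step 5. This stands, and it limits the weight of the point.

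**Conclusion.** The concern holds as a modest design point. The protocol states neither balance of the context order within group nor a position term, although 12 subjects allow exact balance. If the list is unrestricted and position is not modelled, the standard error of a within-group music-sound contrast rises by 4% to 51% over the assumed drifts (3 to 8 points per block) and paired-difference SDs (10 or 15). It rises by nothing if there is no drift. With position modelled, the average cost of an uneven list is about 10% in variance per group and 3% pooled. The within-subject contrasts of Hypothesis 1 and the audio factor lose precision. They are not biased, the sample size stands, and the between-group primary comparison is little affected. Nothing is established about imbalance of skin region.

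**What to change.** - Within each of the three groups, assign each of the six music/sound/silence orders to two subjects, from a permuted list issued together with the group allocation. Each context then falls four times in each position. Group allocation follows the screening and stability checks and the post-test is in the same session, so few slots should be lost. A replacement subject should take the vacated order.
- Add block position as a factor in the repeated-measures model. Both parts are needed: balance alone leaves order variation in the error term, and the term alone leaves the cost of an uneven list.
- State how regions 1-3 map to contexts or positions. If regions are used in sequence, the same list balances region too.

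Cost: a different randomisation list and 2 degrees of freedom. No extra subjects, visits or procedures.

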**Psychological assessments**

We believe that psychological states may be significant factors in pain experience/modulation and may have an impact on analgesia.

Beck Depression Inventory (BDI): The 21-item BDI has shown good sensitivity and specificity for major depression in chronic pain patients28,29. A score greater than 18 will be considered high, and less than 13, low for depression symptoms28.

Expectations for Relief Scale (ERS): The ERS is a 0-10 scale (with 0 indicating a very negative expectation of “does not work at all” and 10 indicating a very positive expectation of “complete pain relief”) used to measure the expectation of treatment pain relief22.

Tellegen Absorption Scale (TAS): TAS measures individual differences in absorption, a trait that involves an openness to experience emotional and cognitive alterations across a range of situations30.  It is a 34-item true-false scales that asks participants to rate the degree to which they become absorbed in everyday imaginative experiences (e.g., viewing a sunset).  It has been widely used in personality research.

Spielberger State-Trait Anxiety Inventory (STAI): STAI consists of two 20-item self-report inventories. It is a rapid but detailed assessment that can distinguish between basal and reactive anxiety. Scores range from 20 to 80 and the higher the score the greater the level of anxiety31. Part 1 (trait) measures basal anxiety will be administered during Session 1 and Part 2 (state) which measures reactive anxiety will be administered pre-post-Session 2. Normative data are available31.

General Self Efficacy Scale (GSES): This is a 10-item psychometric scale that is designed to assess optimistic self-beliefs to cope with a variety of difficult demands in life. In contrast to other scales that were designed to assess optimism, this one explicitly refers to personal agency, i.e., the belief that one's actions are responsible for successful outcomes32.

Rumination Reflection Questionnaire (RRQ): Trapnell and Campbell33 originally developed the RRQ to distinguish between the maladaptive and adaptive components of rumination. Rumination items are based on research findings related to metacognitions and evaluations associated with both anxiety and depression. Items on the reflection subscale are from research associated with the cognitive and motivational tendencies typically linked to openness to experience, curiosity, and interest in abstract or philosophical thinking. Each subscale consists of 12 statements to endorse agreement of.

Brief Mood Introspection Scale (BMIS): Consisting of 16 adjectives, two from each of 8 mood categories, it assesses presentmood and has been shown to have good factor validity and reliability34. We will measure this pre-post-Session 2.

Sensory and Unpleasantness Visual Analog Scale (VAS): This is a simple 0-100 visual scale representing the magnitude of either pain intensity or pain unpleasantness. It has been widely validated and used in studies taking behavioral pain ratings, and instructions are given to subjects on how to distinguish between intensity vs. affective unpleasantness.

Self Assessment Manikin (SAM): A set of three visual scales representing valence, arousal, and perceived control used widely in emotion rating studies.

Final Questionnaire**:** To determine the success of our procedures, we will administer a final questionnaire asking patients whether they believed they had received genuine treatment, how certain they are of the answer, why the treatment might or might not have worked for them, and their final attitudes toward the treatment. We will also ask them various questions about their experience during the procedures.

## **VI. BIOSTATISTICAL ANALYSIS**

**Power Analysis:**
We will study 12 subjects in three groups for a total of 36 subjects; the primary end points are differences between the music/sound conditioning groups and the no conditioning group. In our previous studies for placebo analgesia using a similar model22, 35-37, we observed a SD for pain rating difference of 1.7.  Using this value, with n=12 subjects in each group, we expect 80% power to detect an absolute difference in pain ratings of 2.1 or greater (two sample t-test at the 0.05 two-tailed significance level).

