## **V. STUDY PROCEDURES**

**Overview of Experimental Design**

To accomplish the Specific Aims, a single two-session experiment will be performed with 36 healthy, pain experiment-naïve subjects who will be randomized into 3 treatment groups. The three treatment groups are music conditioning, sound conditioning, and no-treatment routine pain calibration. Primary outcome measures will include the difference (pre- minus post-treatment) in subjective pain rating to calibrated experimental noxious heat stimuli. We will also collect treatment expectations using an Expectancy of Relief Scale (ERS, below) and ratings of subjective responses to treatments assessed through various psychometric scales and surveys for all groups.

The two behavioral sessions will be separated by a minimum of 2 days and a maximum of 10 days. Subjects will be asked to hold common daily activities constant on experiment days (i.e. duration of sleep, eating habits, caffeine intake). Prior to coming to the experimental site, all subjects will be asked to acquire/choose a set of personal music that satisfies certain criteria for the study (see following section). During both sessions, subjects will be receiving sets of calibrated noxious thermal stimuli and after each stimulus will use 0-100 visual analog scales to rate the pain sensation. In the ***first session***, subjects will go through the consent process and screening questions, and we will also determine whether a subject can report consistent, appropriate responses to the application of the calibrated noxious thermal stimuli. This session will last about 120-150 minutes. In the ***second session*** we will repeat testing for appropriate responses to the thermal stimuli – only subjects that perform consistently on the pain rating task (can reliably rate mild intensity pain stimuli as less painful than moderate intensity stimuli and have comparable ratings across sessions - within 1 STD) will continue to further testing during the second session. Subjects who are eligible to continue will be randomized into one of the three treatment groups (N=12/group). These subjects will then receive a modification of a well-characterized conditioning-expectancy manipulation procedure designed to enhance a subject’s expectation of pain relief in response to their assigned treatment. This session will last about 150-180 minutes. At the end of the study all subjects will be de-briefed so that they understand the procedures and why they were used.

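### The power statement gives an SD of 1.7 and a detectable difference of 2.1 without a scale; they do not appear to be 0-100 VAS points, so it does not show that 2.1 VAS points can be detected

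*Protocol*

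**What the plan says.** The sample size is justified in Protocol Section VI, Power Analysis: "We will study 12 subjects in three groups for a total of 36 subjects". The comparison is stated as "the primary end points are differences between the music/sound conditioning groups and the no conditioning group". For the variability, the protocol cites the team's earlier placebo analgesia studies, in which "we observed a SD for pain rating difference of 1.7". From this it concludes: "we expect 80% power to detect an absolute difference in pain ratings of 2.1 or greater", using a "two sample t-test at the 0.05 two-tailed significance level". No unit or scale is attached to the 1.7 or to the 2.1.

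The outcome is the change in pain rating from before to after treatment (Section V, Overview of Experimental Design). The same section fixes the scale: subjects "after each stimulus will use 0-100 visual analog scales to rate the pain sensation". The Session 1 and Session 2 descriptions and the VAS entry under Psychological assessments use the same range. The only 0-10 scale in the protocol is the Expectations for Relief Scale, which measures expectancy, not pain.

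Two further statements show the size of ratings expected. Temperatures are chosen to give "subjective intensity ratings of Moderate = 20-40 and Strong = 60-80", and the baseline and post-manipulation stimuli use one temperature from the low end of the Strong band. In Session 2, the first baseline set "must be within 15% of ratings given during rating stability testing during Session 1".

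**The concern.** Section VI speaks only of pain ratings, and the trial has only one pain-rating range. A reader will naturally take the claim as 2.1 points on the 0-100 VAS, which is 3.5% of a rating of 60 (2.1/60). An SD of 1.7 on that scale would put about 95% of subjects' changes within 3.3 points of the mean (1.96 x 1.7). That sits badly with a protocol that accepts a shift of 9 points or more as stable, and that expects about 25% attrition (Section IV), chiefly because subjects fail to give stable, reliable ratings.

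This calculation is the only support for 12 per group. If its figures belong to a shorter scale, the effect the trial is powered for is not defined in units of its own outcome. A null result could then be misread as evidence against an effect of about 2 VAS points. The missing unit also hides how large an effect the design needs, about 1.2 SD. Section I describes the effects in earlier studies as mostly modest, while hoping that combining music with conditioning will do better.

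**Working it through.** **Inputs.** n = 12 per group, SD 1.7, difference 2.1, two-sided alpha 0.05, two-sample t-test (Section VI). Outcome scale 0-100, Strong band 60-80 and the 15% rule (Section V).

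**1. Reproduce the stated figure.**
- Noncentrality = difference / (SD x sqrt(2/n)) = 2.1 / (1.7 x 0.408) = 3.03, on 22 degrees of freedom.
- Power from the noncentral t distribution is 82.4%. With n = 11 it is 78.7%, so 12 is the smallest whole number per group that reaches 80%.
- The difference detectable with exactly 80% power at n = 12 is 2.03, so 2.03/1.7 = 1.197, or about 1.20 SD.

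The stated calculation reproduces, and 2.1 is slightly conservative.

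**2. Compare 1.7 with the protocol's own VAS figures.**
- 15% of 60 is 9 points; 15% of 80 is 12 points.
- 9/1.7 = 5.3 and 12/1.7 = 7.1.
- Illustration only: shifts spread evenly over plus or minus 9 points would have an SD of 9/sqrt(3) = 5.2.

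The 15% figure is a tolerance between sessions, not an SD of the outcome, so these ratios indicate implausibility and do not estimate the true SD.

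**3. What the design can detect in VAS points.** The documents give no SD on the 0-100 scale, so a range is assumed. The value 8.5 is what 1.7 becomes if it was observed on a 0-20 scale (x 5), and 17 if on a 0-10 scale (x 10). The values 5 and 10 are further illustrations. Detectable difference = 1.197 x SD; power for 2.1 uses the formula in step 1.

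| SD in VAS points | Difference detectable with 80% power | Power for 2.1 VAS points |
|---|---|---|
| 1.7 (as stated, if it were VAS) | 2.03 | 82% |
| 5 (assumed) | 6.0 | 17% |
| 8.5 (if source scale 0-20) | 10.2 | 9% |
| 10 (assumed) | 12.0 | 8% |
| 17 (if source scale 0-10) | 20.3 | 6% |

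**4. Rescale both figures together.** Power depends only on the ratio of difference to SD. With 10.5 and 8.5, or 21 and 17, the ratio is still 2.1/1.7 = 1.24 and power is still 82.4%.

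**The case against.** The strongest defence is that nothing was miscalculated. The stated power reproduces, and step 4 shows that it survives any common change of scale. The low powers in the table arise only when the SD is rescaled and 2.1 is left alone, and Section VI never says that 2.1 is in VAS points. All of that stands. A reader might infer that the 80% is false or that the arithmetic is wrong; the documents support neither.

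A reader might also infer that the figures cannot be VAS points and were certainly carried over unconverted. That too goes beyond the documents. The protocol does not state the rating scale of the earlier studies, so the 0-10 and 0-20 cases are assumptions.

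The internal evidence is indirect as well. The 15% rule is an eligibility limit comparing Session 2 with Session 1, whereas the outcome is a change within Session 2. The 20-point width of the Strong band concerns the level of ratings, and differences in level between subjects largely cancel in a within-subject difference. Neither measures the SD of change.

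What the defence does not remove is that the one stated detectable difference has no unit, in a trial whose pain ratings all run from 0 to 100, and that reading it as VAS points requires an SD which the surrounding figures make implausible. Nor is this a detail left for a statistical analysis plan, because the protocol itself states the number and relies on it.

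**Conclusion.** The point holds as a defect of scale in the power statement. The 80% power is sound for a standardized effect of about 1.2 SD with 12 per group. It does not support a claim to detect 2.1 points on the 0-100 VAS. Over the assumed SDs of 5 to 17 points, the difference detectable with 80% power is about 6 to 20 points, and power for 2.1 points is about 17% down to 6%.

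This rests on one inference: that 1.7 is not in VAS points. The 15% tolerance at ratings of 60 or more, and the attrition expected from unstable ratings, make that likely but do not prove it. If the sponsor confirms that 1.7 was observed on a 0-100 scale, the stated figure stands and only the unit needs adding. It would be wrong to conclude from this point that the sample size was miscalculated or must be increased.

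**What to change.** In Section VI, Power Analysis:

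- Name the scale on which the SD of 1.7 was observed.
- Express that SD in 0-100 VAS points.
- Give the difference detectable with 80% power at 12 per group as 1.20 x that SD, in VAS points.
- Replace the 2.1 threshold with that figure, unless the SD is confirmed to be on a 0-100 scale.

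Keep 36 subjects. The cost is a sentence or two and no extra recruitment. The downside is that the stated detectable difference becomes less favourable, for example about 20 points instead of 2.1 if the source scale was 0-10.
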